## Abstract

**Background:**

Subjective cognitive decline (SCD) is an early manifestation of Alzheimer’s disease (AD) and offers a therapeutic window where interventions have strong potential to prevent or delay the progression of AD. Aerobic exercise and cognitive training represent two promising interventions for AD prevention, but their synergistic effect has yet to be assessed in persons with SCD.

**Methods/design:**

The purpose of this single-blinded, 3-parallel group randomized controlled trial is to test the synergistic efficacy of an exergame intervention (simultaneous moderate-intensity aerobic cycling and cognitive training) on cognition and aerobic fitness in community-dwelling older adults with SCD. The Exergames Study will randomize 96 participants on a 2:1:1 allocation ratio to 3-month exergame, cycling only, or attention control (stretching). Primary outcomes include global cognition and aerobic fitness, which will be assessed at baseline and after 3 months. The specific aims of the Exergames Study are to (1) determine the efficacy of the exergame in older adults with SCD and (2) assess the distraction effect of exergame on aerobic fitness. Data will be analyzed using ANOVA following intention-to-treat.

**Discussion:**

This study will test the synergistic effects of exergame on cognition and aerobic fitness. It has the potential to advance prevention research for AD by providing effect-size estimates for future trials.

**Trial registration:**

ClinicalTrials.gov NCT04311736. Registered on 17 March 2020.

## Background

Subjective cognitive decline (SCD), the subjective experience of worsening memory or cognitive, is one of the earliest noticeable symptoms of Alzheimer’s disease (AD) [1]. It offers a therapeutic window where interventions have strong potential to prevent or delay the progression of AD because of the increasing recognitions that AD pathology accumulates over years to decades before any observable clinical symptoms [2]. Interventions at later clinical phases of AD have been ineffective or shown only modest benefits [3]. Aerobic exercise and cognitive training are two potential disease-modifying interventions through the induction of brain plasticity and attenuation of AD neurodegeneration [4–6]. Epidemiological studies have linked exercise to reduced risk for AD [7–9]. Likewise, randomized controlled trials (RCT) and meta-analyses of RCTs demonstrate that aerobic exercise produced mild to moderate gains in a wide range of cognitive domains in persons with intact cognition, mild cognitive impairment (MCI), or dementia [10–15]. On the other hand, cognitive training involves repeated practice of a set of standard cognitive tasks targeting specific cognitive domains [16]. Targeting cognitive processes (e.g., attention) may produce more robust and broadly generalizable effects than targeting cognitive structures (e.g., delayed recall) [17, 18]. Previous studies found that such process-based cognitive training generated a moderate to large improvement in selected cognitive domains in older adults with intact cognition or MCI [19–21].

Given that aerobic exercise and cognitive training work through discrete neuronal mechanisms, combined aerobic exercise and cognitive training might have a synergistic and superior effect on cognition compared to either intervention alone [22]. Traditionally, the combined effects of exercise and cognitive training have been investigated in a sequential manner, producing mixed results [6, 23–27]. It is thought that the heterogeneity between the interventions and the delivery of the interventions (i.e., sequentially) may be the primary factors for the inconsistencies [28, 29]. A second interventional delivery option is simultaneous (dual-task) exercise + cognition training (i.e., “exergame”); however, there are limited studies that have investigated this delivery modality [29]. Anderson-Hanley [30] reported results from an exergame intervention (i.e., the “Cybercycle” Study) (cycling + virtual reality path finding and competition with a shadow cycler), a multi-site cluster RCT in which the cognitive benefıt of cybercycling showed superior cognitive effects than traditional stationary cycling, for older adults living independently. More recently, Barcelos [28] compared cycling alone to virtual cycling with a concurrent video game task and found greater effects on cognitive measures from the cycling plus gaming intervention. However, similar studies have not been conducted in older adults with SCD.

### Study aims

The purpose of this phase II RCT is to test the efficacy and additive/synergistic effects of an exergames intervention (simultaneous moderate intensity cycling and cognitive training), in comparison to cycling only and attention control (stretching) on cognition and aerobic fitness in older adults with SCD. The specific aims and hypotheses of the study are described as follows:
Aim 1: Determine the efficacy of the exergame in older adults with SCD.Hypothesis: Exergame will improve global cognition more than cycling only and attention control.Aim 2: Assess the distraction effect of an exergame on aerobic fitness.Hypothesis 2a: Exergame participants will achieve similar gains in aerobic fitness to cycling participants.Hypothesis 2b. Exergame participants will achieve similar exercise intensity targets to cycling participants.

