## Methods

### Design

The RCT will use a single-blind, 3-parallel group design, guided by CONSORT [31] and SPIRIT [32] guidelines (*n* = 96). We will use a 2:1:1 allocation ratio to randomize 48 subjects to exergame, 24 to cycling only, and 24 to attention control within age strata (< 75 and ≥ 75 years) and using permuted blocks of 4 and 8 participants. Based on our previous studies, we anticipate screening approximately 288 individuals to enroll 96 participants. Cognition and aerobic fitness will be assessed at baseline and 3 months. This study was approved by the university Institutional Review Board and registered at ClinicalTrials.gov on 17 March 2020 (study identifier NCT04311736).

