#### Exergame

Subjects will cycle as described in the cycling protocol while engaging in cognitive training for the duration of cycling. Cognitive training will include one level of difficulty with six task scenarios in the context of three virtual worlds (environments): “Small-Town Downtown,” “Underwater World,” and “Wild West.” For example, the virtual world of “Small-Town Downtown” will be composed of shops, restaurants, storefronts, and office buildings. Each environment will be open-world and static and will not change over time or between game sessions. This will allow the participant to memorize the layout over multiple play sessions. Visual cues (“Landmarks”) will serve as memorization guides for navigation. Landmark examples for “Small-Town Downtown” include unique buildings, bridges, statues, parks, and other true-to-the-environment objects. Scenarios will have high ecological validity. Scenario examples in “Small-Town Downtown” include (1) picking up and dropping off a delivery for a friend, (2) visiting the post office to mail a letter, (3) sorting books at the library, and (4) going shopping at the grocery store. In each of the environments, the participant must follow directions and navigate to a destination where the cognitive task will be performed. For each scenario, participant start position within the environment will be randomly assigned by the system. A scenario-specific cognitive task will be triggered. The game will inform the participant of the assigned task and, automatically, determine and inform the participant of the fastest route from the starting point to the scenario destination where the task will be performed. The participant will be required to remember the assigned task, follow the directions and navigate to the destination, and then remember what action is required to complete the task. The participant will move forward through the environment by pedaling the stationary cycle. Left and right turns along the route will be input by the participant through buttons on the game controller. To enable a smooth transition into the cognitive task while maintaining cycling movement, the game’s camera will continue to progress in a forward direction to match participant pedaling speed, while the level environment fades into a desaturated surreal version of each scenario’s setting.

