#### Attention control

Participants will participate in passive stretching that we have previously tested [48, 49] and that are matched to session durations for cycling and exergame groups. Light intensity (RPE ≤ 9 or HRR ≤ 30%) stretching exercises include seated movements and static stretches that induce no changes in aerobic fitness.

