## Discussion

Developing interventions, with strong potential to prevent or delay the onset of AD in persons with SCD is critical. Aerobic exercise and cognitive training represent two promising interventions; however, their synergistic effects on preventing AD have not been evaluated. Our study will develop a novel, apple-TV, and iPad-based cognitive training that is immersive, naturalistic, and similar in tasks to real life, and therefore increases the ecologic validity of the treatment [29]. It is cognitively challenging but also increases exercise enjoyment.

All attempts have been undertaken to ensure the highest quality of study design and delivery of the Exergames Study. First, RCTs are considered the gold standard design for determining the causal effect of an intervention on an outcome. Alternatively, intervention trials commonly employ usual care or waitlist control groups or cross-over design. Usual-care or waitlist controls preclude assessing the Hawthorne or placebo effect of exergames, while cross-over designs are ideal for interventions without carry-over effects, which is also not the case for exergames. In addition, we have built in four strategies to prevent unblinding, another potential problem occurring in RCTs. The four unblinding prevention strategies include (1) assessors will not interact with other staff who are not blinded (i.e., exercise interventionists) and will participate in separate meetings, (2) investigators will be blinded to group assignments, (3) participants will be blinded to the study aims and reminded as needed not to discuss their experiences with the outcome assessor, and (4) randomization will be completed using permuted blocks. Additionally, age is a known, strong factor affecting cognition. While our aims are not focused on age, we will stratify enrollment by age to equalize age distribution across groups [55, 56].

In summary, the Exergames Study will be the first RCT to examine the additive/synergistic effects of a novel simultaneous moderate intensity, supervised aerobic exercise + cognitive training intervention on cognition and aerobic fitness. This study looks to advance AD prevention research by providing precise immediate and long-term effect-size estimates of an aerobic exercise intervention delivered with simultaneous cognitive training to inform future fully powered, large scale phase III RCTs.

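### The article says the trial tests synergistic effects, but without a cognitive-training-only arm neither synergy nor strict additivity on cognition can be estimated

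*Protocol article*

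**What the plan says.** Four places in the Protocol article present synergy as something the trial will test or examine:

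- Abstract, Methods/design: the purpose is to "test the synergistic efficacy of an exergame intervention (simultaneous moderate-intensity aerobic cycling and cognitive training".
- Abstract, Discussion: "This study will test the synergistic effects of exergame on cognition and aerobic fitness".
- Study aims, purpose: "test the efficacy and additive/synergistic effects of an exergames intervention (simultaneous moderate intensity cycling and cognitive training), in comparison to cycling only", with stretching as the second comparator.
- Discussion, closing paragraph: the study "will be the first RCT to examine the additive/synergistic effects" of the combined intervention.

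The Design section will "randomize 48 subjects to exergame, 24 to cycling only, and 24 to attention control". The Exergame section defines the combined arm: "Subjects will cycle as described in the cycling protocol while engaging in cognitive training for the duration of cycling". The control arm gets stretching: "Participants will participate in passive stretching that we have previously tested". No arm gets cognitive training without cycling.

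The Aim 1 hypothesis is narrower than the purpose: exergame is to do better on global cognition than each of the other two arms. Statistical analyses plans a three-group ANOVA followed by Tukey or Games-Howell comparisons, with no interaction contrast. The article does not acknowledge the absence of a training-only arm as a limit.

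**The concern.** Synergy means that the combination does more than the sum of its parts. Strict additivity means that it does exactly the sum. Either statement needs the effect of each part alone, and here one part is never given alone.

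The risk lies in how a positive result would be read. The Background section cites mild to moderate cognitive gains from aerobic exercise, and moderate to large gains in selected domains from process-based cognitive training, in people with intact cognition or mild cognitive impairment. If training has a similar effect in subjective cognitive decline, exergame should beat cycling through training alone, with no interaction at all. The stated purpose invites that same result to be reported as synergy. The Discussion intends the results to inform phase III trials, where whether the combination beats cognitive training alone would be a natural design question. This trial leaves it open.

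**Working it through.** **Inputs.** Arms and allocation of 48, 24 and 24 come from Design. Arm contents come from Exergame, Cycling group and Attention control. Attrition of 12%, power of 80% and an effect size of 0.85 come from Sample size and power. Alpha of 0.05 comes from Statistical analyses; two-sided testing is assumed, since the article does not say.

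**1. The plan's own figure.** Evaluable numbers are 48 × 0.88 ≈ 42 and 24 × 0.88 ≈ 21. The standard error of exergame minus stretching, in SD units, is √(1/42 + 1/21) = 0.267, so the noncentrality is 0.85 / 0.267 = 3.18. Power is 87.9% unadjusted, 80.9% at a two-sided alpha of 0.025, and 78.4% with Tukey's critical value for three groups and 81 degrees of freedom. The stated 80% is thus roughly reproduced with a multiplicity adjustment. It concerns exergame against stretching only.

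**2. What the three arms identify.** Write the mean cognitive response relative to stretching as:

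| Cell | Mean | Randomized? |
|---|---|---|
| Stretching | 0 | yes |
| Cycling | C | yes |
| Cognitive training alone | T | no |
| Exergame | C + T + I | yes |

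I is the interaction: positive for synergy, zero for additivity, negative for antagonism. The available contrasts are:

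- cycling − stretching = C
- exergame − cycling = T + I
- exergame − stretching = C + T + I

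The cell-mean model has four parameters (intercept, C, T, I), but its design matrix has rank 3 in these cells. C and T + I are estimable; T and I separately are not. Exergame against training alone would be (C + T + I) − T = C + I, which is not estimable either. Adding the missing cell gives rank 4.

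**3. Illustration.** The values below are chosen for the example and are not in the article. Each gives exergame − cycling = 0.5 SD:

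| T | I | Reading |
|---|---|---|
| 0.5 | 0 | additive |
| 0.2 | +0.3 | synergy |
| 0.7 | −0.2 | antagonism |

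More participants would estimate the 0.5 more precisely, but would not choose among the rows.

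**4. What a fourth arm would take.** The interaction contrast is exergame − cycling − training + stretching.

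- 96 participants over four equal arms, 21 evaluable in each: SE = √(4/21) = 0.44 SD. The detectable interaction at 80% power is about 1.24 SD, and power for an interaction of 0.85 SD is about 49%.
- A training arm of 24 added to the present trial (120 in total): SE = √(1/42 + 3/21) = 0.41 SD, detectable interaction about 1.15 SD.
- 80% power for an interaction of 0.85 SD: 4 × [(1.96 + 0.84) / 0.85]² ≈ 43.5, so 44 evaluable per arm and 176 / 0.88 = 200 enrolled.

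The 0.85 SD interaction is an assumption that borrows the plan's effect size; the article gives no interaction size.

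**The case against.** The strongest reply is that no operative part of the trial rests on synergy. The specific aims, the power statement and the planned comparisons concern efficacy against two comparators and a distraction effect on fitness. That stands: the fault is in the stated purpose and intended conclusion. A reader might infer that the trial cannot meet Aim 1, but the documents do not support this, because both Aim 1 contrasts are estimable.

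Three further limits also stand.

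- *Additive* can fairly be read as added benefit over cycling, particularly as the Study aims sentence names the comparators. Exergame minus cycling estimates that directly. Only the factorial sense fails.
- The argument is strong for cognition and weaker for fitness. If cognitive training without pedalling does not change shuttle-walk distance (T = 0, an assumption the article does not state), exergame minus cycling on fitness is the interaction itself, which is close to what Aim 2 calls distraction. Hypothesis 2a expects gains similar to cycling, so it does not predict synergy on fitness.
- The Background remark that combined training "might have a synergistic and superior effect on cognition compared to either intervention alone" is rationale, hedged and cited. A reader might take it as a promised comparison with each component, but it is not stated as a trial objective. The Abstract's Background sentence likewise describes a gap in the literature.

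What does not stand is the idea that an unseen analysis plan could settle the matter. The article itself fixes the arms, and no analysis of three cells identifies the fourth.

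**Conclusion.** The purpose is wrong as written. The Abstract (Methods/design and Discussion), Study aims and the closing Discussion claim a test of synergistic or additive/synergistic effects that the three arms cannot provide for cognition. This is a failure of identification, not of power. It needs no assumption beyond the arm contents as described and the usual definitions of synergy and additivity.

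The effect of exergame against stretching, the effect of cycling against stretching, and the increment of exergame over cycling all remain estimable. A reader might infer that the design is invalid or that a fourth arm is required. Neither follows: the stated hypotheses can be tested with the arms as they are, and it is the claim that has to change.

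**What to change.** Keep the three arms, the outcomes and the analysis.

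1. Replace *synergistic efficacy* (Abstract, Methods/design), *synergistic effects* (Abstract, Discussion) and *additive/synergistic effects* (Study aims; Discussion, closing paragraph) with: *the effect of exergame versus stretching and its incremental effect over cycling alone*.
2. State as a limitation that this increment cannot be split into a cognitive-training effect and an interaction, and that superiority to cognitive training alone is not tested.
3. Draw no synergy conclusion from the results.

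The Background sentences may stay as rationale.

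The cost is wording and a less ambitious claim. The alternative is a training-only arm with a prespecified interaction contrast and a sample size for it. That would need about 200 participants under the illustrative 0.85 SD interaction, against 96 planned, in a trial already open for enrolment.

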## Methods

### Design

The RCT will use a single-blind, 3-parallel group design, guided by CONSORT [31] and SPIRIT [32] guidelines (*n* = 96). We will use a 2:1:1 allocation ratio to randomize 48 subjects to exergame, 24 to cycling only, and 24 to attention control within age strata (< 75 and ≥ 75 years) and using permuted blocks of 4 and 8 participants. Based on our previous studies, we anticipate screening approximately 288 individuals to enroll 96 participants. Cognition and aerobic fitness will be assessed at baseline and 3 months. This study was approved by the university Institutional Review Board and registered at ClinicalTrials.gov on 17 March 2020 (study identifier NCT04311736).

### Setting

Screening and data collections will occur in a private room at the Clinical and Translational Science Institute or Laboratory of Clinical Physiology at the University of Minnesota, local Young Men’s Christian Association (YMCA) gym, or senior center in close proximity to participant’s residence. The interventions will occur at a local YMCA gym, senior center, or the participant’s residence.

### Study population

#### Recruitment

We plan to enroll 96 participants with a proactive recruitment plan, including presentations at local YMCAs and senior living facility partners, exhibits at relevant conferences, mass email sends, advertisements through social media (i.e., Facebook and Instagram), and recruitment material distributions (i.e., fliers) in the communities.

#### Eligibility and screening

Potential participants who respond to our recruitment strategies and initiate contact with us will be carefully screened for eligibility and exercise safety using a three-step procedure spread over the course of 2–4 weeks, including a phone interview, an in-person interview, and a shuttle walk test (SWT) to ensure they meet our eligibility criteria (Table 1).
Phone interview: The staff will receive the respondent’s verbal consent for participating in a 20–30-min phone interview. The phone interview will evaluate the presence of SCD, health history, contraindications to exercise [33], and cognitive status (telephone interview for cognitive status (TICS)) [34]. Potential participants who are not excluded based on the phone screen will be scheduled for an in-person interview.In-person interview: Informed consent, Health Insurance Portability and Accountability Act (HIPAA) authorization, and permission for release of medical records will be obtained by study staff. During informed consent, individuals will be informed about the study procedures, compensation, time commitment, potential risks and benefits, compensations, data collection, the voluntary nature of study participation, and contact within and outside the study team for human subjects. The study staff will corroborate phone screen data; administer questionnaires including Geriatric Depression Scale (GDS) [35], Beck’s Anxiety Inventory (BAI) [36], and Geriatric Anxiety Scale (GAS-10) [37]; and conduct a focused physical assessment. The study coordinator will summarize screening data for review by the investigators to determine eligibility. For eligible participants, letters will be sent to the potential participant’s medical providers to obtain medical clearance for exercise and for excluding the contribution of psychological symptoms to SCD.Shuttle walk test (SWT): Upon receiving exercise safety clearance, participants will complete a SWT to further rule out clinical signs and symptoms indicative of symptomatic cardiovascular disease and to obtain peak heart rate (HR) to be used for purposes of exercise prescription. Resting seated and standing HR and blood pressure will be evaluated to ensure safety prior to performing the test. HR will be continuously monitored during exercise. The test will be stopped if any clinical signs or symptoms develop [33]. HR and blood pressure will be monitored for 6 min following completion of the SWT to ensure residual stability. Those who successfully complete the SWT (i.e., develop no signs and symptoms of symptomatic cardiovascular disease) will be formally enrolled in the study upon completing baseline data collection and subsequently randomized.

**Table 1 Tab1:** Eligibility criteria

Inclusionary criteria	Exclusionary criteria
a) Subjective Cognitive Decline (SCD: defines as answering yes to the question’s “Do you perceive memory or cognitive difficulties?” and “In the last two years, has your cognition or memory declined”) b) Not engaging in aerobic exercise or cognitive training > 2 days/week, 30 min a session for the past 3 months c) Age 65 years and older d) Ability to provide written consent e) English speaking	a) Resting heart rate > 100 or < 50 beats/min with symptoms b) Dementia or mild cognitive impairment (self-report, diagnosis, or scoring < 26 on the TICS c) Neurological or major psychiatric disorder likely causing SCD d) Alcohol or chemical dependency that likely is causing SCD e) Current enrollment in another intervention study f) ACSM contraindications to exercise or other factors that make exercise impossible or unsafe g) Inability to read due to illiteracy or poor eyesight

*ACSM* American College of Sports Medicine, *TICS* Telephone Instrument for Cognitive Status

